## Abstract

**Background:**

Serious and often lasting vision impairments affect 30% to 35% of people following stroke. Vision may be considered the most important sense in humans, and even smaller permanent injuries can drastically reduce quality of life. Restoration of visual field impairments occur only to a small extent during the first month after brain damage, and therefore the time window for spontaneous improvements is limited. One month after brain injury causing visual impairment, patients usually will experience chronically impaired vision and the need for compensatory vision rehabilitation is substantial.

**Objective:**

The purpose of this study is to investigate whether rehabilitation with Neuro Vision Technology will result in a significant and lasting improvement in functional capacity in persons with chronic visual impairments after brain injury. Improving eyesight is expected to increase both physical and mental functioning, thus improving the quality of life.

**Methods:**

This is a prospective open label trial in which participants with chronic visual field impairments are examined before and after the intervention. Participants typically suffer from stroke or traumatic brain injury and will be recruited from hospitals and The Institute for the Blind and Partially Sighted. Treatment is based on Neuro Vision Technology, which is a supervised training course, where participants are trained in compensatory techniques using specially designed equipment. Through the Neuro Vision Technology procedure, the vision problems of each individual are carefully investigated, and personal data is used to organize individual training sessions. Cognitive face-to-face assessments and self-assessed questionnaires about both life and vision quality are also applied before and after the training.

**Results:**

Funding was provided in June 2017. Results are expected to be available in 2020. Sample size is calculated to 23 participants. Due to age, difficulty in transport, and the time-consuming intervention, up to 25% dropouts are expected; thus, we aim to include at least 29 participants.

**Conclusions:**

This investigation will evaluate the effects of Neuro Vision Technology therapy on compensatory vision rehabilitation. Additionally, quality of life and cognitive improvements associated to increased quality of life will be explored.

**Trial Registration:**

ClinicalTrials.gov NCT03160131; https://clinicaltrials.gov/ct2/show/NCT03160131 (Archived by WebCite at http://www.webcitation.org/6x3f5HnCv)

## Introduction

Worldwide, stroke is the second most common cause of death and the third most common cause of disability [1]. Serious and often lasting vision impairments affect 30% to 35% of people with stroke [2]. In general, vision may be considered the most important sense in humans, and even small permanent deficits can dramatically affect the quality of life.

Lack of vision (anopia) after brain damage limits rehabilitation and enhances other invalidating effects. Impaired vision results in impaired balance, increased risk of serious falls, increased support needs, reduced quality of life and an impaired ability to perform activities of daily living [3]. Recovery of visual field deficits occurs primarily and only to a modest extent the first month after brain injury [4], and thus the time window for spontaneous improvements is very limited. Hence, brain-impaired persons with visual impairment will most likely experience chronically impaired vision already 4 weeks after brain injury, and the need for visual compensatory rehabilitation is substantial [4].

Neuro Vision Technology is a supervised training course where people with visual field deficits are trained in compensatory and restorative techniques. The course includes a special computer program, a light panel and a special training program, and the course is conducted by occupational therapists with Certified Orientation & Mobility Instruction (O&M instructors) with visual expertise [2]. Through the Neuro Vision Technology course, the individual’s specific vision deficits are carefully identified through a five-step program. Personal data is used to organize individual training and thereby teaching the individual to cope with situations that cause problems in everyday life. In spite of reported positive results of Neuro Vision Technology training among several individuals [5], there are currently no scientific studies [2] on whether rehabilitation with Neuro Vision Technology results in lasting and clinically significant improvements in people with severe and chronic visual field impairments.

The aim and hypothesis of this study is to test whether rehabilitation with Neuro Vision Technology can lead to significant and lasting improvements in persons with chronic visual impairments after brain injury. Improving eyesight is expected to increase both physical and mental functioning, thus improving the quality of life. Study participants will be investigated in terms of both visual and mental functions, including quality of life, cognition and depression.

## Methods

This study is designed as a prospective study in which the same subject is examined before and after the intervention.

### Participants

Participants are suffering from chronic visual field impairments; thus, participants will not experience significant spontaneous remission or deterioration. Participants have typically experienced a stroke (ischemic or hemorrhagic) or traumatic brain injury. There is a high risk of injury worsening in participants with malignant or progressive tumors, making it difficult or impossible to document a beneficial effect of the intervention; Participants with such progressive diseases as well as participants worsening (eg, from secondary strokes and with further visual impairment) will be excluded from participation in the trial.

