### Blinding

Participants are not randomized as there is only an intervention group and no controls. As far as possible, it is ensured that the investigator who measures the subjects' functional level at the end of intervention has not previously had contact with, or knowledge of, the particular participant. Thus, the level of function of participants is evaluated by different persons before and after intervention to ensure impartial assessments.

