### Statistical Analysis

Data comparisons of ranks before and after performances are calculated using Wilcoxon non-parametric test and optionally categorical variables with chi-2 test. Nonlinear correlations will be evaluated using the Spearman Rank correlation coefficient. Unused or incomplete data is not included in the statistical evaluation and is treated as missing data (ie, no calculations are made using such data). Lack of data is acceptable as long as an assessment of the primary endpoint is still possible. Data from participants that make it possible to assess the primary endpoint will be used as a minimum; however, we hope that data from all subjects can be used to evaluate secondary effect targets. *P* values of less than .05 will be considered significant.

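### Excluding participants who worsen or have a new brain injury or significant disorder after inclusion is one-sided and overstates the before-after change among all enrolled

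*Protocol article*

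**What the plan says.** Three parts of the protocol article bear on this.

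- **Participants.** The section assumes that "participants will not experience significant spontaneous remission or deterioration". It then excludes people with malignant or progressive tumours, whose likely decline is described as "making it difficult or impossible to document a beneficial effect of the intervention". The same sentence goes on: "participants worsening (eg, from secondary strokes and with further visual impairment) will be excluded from participation in the trial".
- **Eligibility textbox.** Among the exclusion criteria is a new brain injury, or another significant disorder, that appears once the person is already in the study.
- **Blinding and Statistical Analysis.** The design is a single arm: "there is only an intervention group and no controls". For the test, "Data comparisons of ranks before and after performances are calculated using Wilcoxon non-parametric test". On the analysis set, "Data from participants that make it possible to assess the primary endpoint will be used as a minimum", and "Lack of data is acceptable as long as an assessment of the primary endpoint is still possible".

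**The concern.** Read alone, the sentence under Participants could be a screening rule. The textbox rules that out for new events: something that happens after inclusion cannot be known at screening, so the criterion removes people who are already enrolled.

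The removal goes one way. A participant who declines because of a second stroke is taken out. A participant who improves for reasons unrelated to the course stays in. In a controlled trial, a comparator would lose people under the same rule and part of the distortion would cancel. Here the before-after change is the whole result, so the selection passes straight into it.

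The rule also undercuts the design's own justification. A before-after comparison without controls relies on the stated absence of material spontaneous deterioration. If those who deteriorate are removed, the analysed data will agree with that assumption whether or not it is true.

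**Working it through.** **Inputs from the protocol article (Sample Size Estimation, Statistical Analysis).** 40% of targets identified at baseline and 65% six weeks after the course, so a planned change of 65 - 40 = 25 points. 23 participants, raised to 29 (23 x 1.25 = 28.75, rounded up). Wilcoxon test, P < .05.

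**Not in the documents, so assumed.** The share of enrolled participants removed after worsening (q), how far they worsen (d, in points), and the distribution of changes. The article has no figure for the effect of the exclusion, so there is none to reproduce.

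**Step 1: effect on the estimate.** Let m be the mean change in those retained. Then:

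- all-enrolled mean = (1 - q) x m - q x d
- overstatement = m - all-enrolled mean = q x (m + d)

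With m = 25:

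| q | d | All-enrolled gain | Overstatement |
|---|---|---|---|
| 5% | 10 | 0.95 x 25 - 0.05 x 10 = 23.25 | 1.75 |
| 5% | 40 | 0.95 x 25 - 0.05 x 40 = 21.75 | 3.25 |
| 10% | 10 | 0.90 x 25 - 0.10 x 10 = 21.5 | 3.5 |
| 10% | 40 | 0.90 x 25 - 0.10 x 40 = 18.5 | 6.5 |

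Of 29 enrolled, 5 to 10% is 1.45 to 2.9 people, so one to three. The overstatement is positive whenever those removed did worse on average than those kept.

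**Step 2: effect on the false-positive rate.** Simulation with 29 enrolled, normal changes, no true effect, and a two-sided Wilcoxon signed-rank test at .05, counting significant results in the direction of improvement (20,000 replicates).

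| Rule | Removed | Mean shift | False improvement |
|---|---|---|---|
| Nobody removed | 0 | 0 | about 2% |
| Lowest observed changes removed | 2 | 0.13 SD | about 11% |
| Lowest observed changes removed | 4 | 0.24 SD | about 26% |
| Removed for an event unrelated to training or to the other sources of change | 2 or 4 | about 0 | 2 to 3% |

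A t-test in place of the Wilcoxon test would give about 13% and 32% in the second and third rows. The Wilcoxon figures are the relevant ones because that is the planned test.

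The second and third rows are an upper bound, because they select exactly on the endpoint score. The last row is the other end: removing people for an unrelated event leaves a random sample of the remaining changes, so the test keeps its level. Where the trial falls between the two depends on how worsening is judged, and the article does not say. Its example includes further visual impairment, which is close to what the mobility route measures.

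**The case against.** The strongest reply is that the article excludes on clinical events and disease, not on a poor re-test score. A second stroke has nothing to do with the training, and leaving such a person out gives a fair answer to a different question: the change in people who stay neurologically stable. The last row of the simulation supports this, since there is then no inflation of false positives. With few events the bias is also modest beside 25 points. All of this stands. It limits the size of the problem, but it does not make the exclusion neutral for the change among all enrolled, and the open-ended category of worsening is not confined to unrelated events.

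Three stronger readings may tempt a reader, and the documents do not support them.

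- *The exclusion will by itself produce a significant result with no real effect.* That requires worsening to be judged from function or vision. The text does not say that it is.
- *Every analysis is restricted to complete cases, so the expected dropout of up to 25% adds to the upward bias.* It is true that "Unused or incomplete data is not included in the statistical evaluation and is treated as missing data", but participants lacking only secondary data are kept, and the sample-size section attributes dropout to age, transport and the time the course takes. The direction of any bias from that dropout is not known. A calculation that turns 25 points into 19 (25 x 22/29) assumes that all seven dropouts gain nothing, which is an assumption and not a finding.
- *Worsening participants are removed because they would obscure a benefit.* That reason is given for malignant or progressive tumours. The sentence then extends the exclusion to worsening participants without repeating it.

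**Conclusion.** The point holds: the article states an exclusion after enrolment that can act in only one direction, in a design with no control arm. For the change among all enrolled, the direction of bias is clear. Its size cannot be fixed from the documents. Under the assumed 5 to 10% removed after worsening by 10 to 40 points, the overstatement is about 2 to 6.5 points against a planned 25. Inflation of false-positive improvement is conditional: none if removals are for events unrelated to training, and at most about 11% or 26% for 2 or 4 removals of 29 if selection were exactly on the outcome. The upper figures should not be read as the expected error rate of this trial.

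**What to change.** 1. Reword the Participants section and the eligibility textbox so that these exclusions refer to status at screening only. This concerns the analysis set; it says nothing on whether a participant with a new event continues training.
2. Define the primary analysis set as everyone with a baseline mobility-route score who starts the course. Use the re-test wherever it can be obtained, whether or not the participant worsened or had a new event.
3. Report the analysis without participants who had a new brain injury as a labelled sensitivity analysis.
4. Add one conservative signed-rank sensitivity analysis for participants whose re-test is missing after worsening or a new event, for example with the missing change given the worst rank.

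Imputing every missing re-test, including those lost to age or transport, is a trade-off and not needed to repair this point.

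The cost is a change of wording, an effort to obtain re-tests after an event, and one or two extra analyses. No more participants are needed. The estimate may be somewhat less favourable.

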### Recruitment

Suitable subjects are consecutively included from the Institute for Blind and Partially Sighted, Herlev University Hospital (especially Neurological Department N108), and other neurological departments (see Textbox 1). A screening will be performed to assess the suitability of a person to participate in the trial. Attendance is voluntary and all sessions are free for the participant. Written consent is required.

### Neuro Vision Technology Intervention and Mobility

The term “orientation & mobility” is understood as the ability to move safely in physical space and in the surrounding community. By controlling orientation and mobility techniques, a person with a restricted field of vision can be able to move not only safely, but also freely and independently. The Neuro Vision Technology method uses a special device in the form of light panels and neurological vision tests providing an overview of visual and cognitive difficulties. The light panel is connected to a computer, and an example showing the setup together with a male participant and a female investigator can be seen in Figure 1. Study participants are then placed at the light panel, where the scan pattern is automated and gradually transferred to indoor mobility routes. When the procedures are automated, the exercise is done outdoors using progressively increasing complexity.

A Neuro Vision Technology course includes 3 hours of cognitive (baseline) testing, then a total of 22 hours of teaching and training given 1.5 hours twice a week for 2.5 to 3 months. Participants are provided with about four weeks of dynamic scanning training using the Neuro Vision Technology scanning device and about four weeks of mobility training using Neuro Vision Technology.

Dynamic scanning is investigated using the special light panel with 24 light bulbs divided into two rows, the panel length is corresponding to the 180 degrees that normal and well-functioning human eyes can see. When considered relevant, a participant is referred to an ophthalmologist, specialist optician, or a reading/visual clinic to ensure the optimal starting point for using the participant’s vision. Records are obtained and used to store test results.

Initially the Neuro Vision Technology assessment process uses presentations of a single light to determine a participant’s ability to perform spontaneous scanning of the affected field, and the participant’s degree of visual field loss. Then the participant will perform exercises with different complexities using sequences of multiple lights. A participant’s response to an exercise indicates his or her ability to attend to multiple stimuli, to systematically search the visual fields and how fast each participant is able to detect changes in the visual field. The Neuro Vision Technology is used to teach each participant visual search strategies from the perimeter of the affected visual field towards the intact visual field.

EligibilityInclusion criteria14 years or older with brain injurypersons with significant vision impairmenteye sight must be 6/18 or betterthe time from symptoms onset to study inclusion is between 12 weeks and 3 yearsExclusion criteriasevere cognitive dysfunctionpersons with anosognosia or severe neglectinability to move independently at least 35 meters with or without assistance, including wheelchairsinability to understand Danish or with communication disorders that prevent participation in teststerminal disorder, other progressive disordersignificant abuse of alcohol or euphoric or narcotic drugsserious disorders such as mental illness, especially severe depressionnew brain injury or other significant disorders emerging after study inclusionimpaired vision not due to brain damage, where the disorder is not considered to be permanent or where the field of vision does not cause significant disability

**Figure 1 figure1:**
[figure not shown]
An example of NVT training, where a brain damaged participant in need of vision rehabilitation is given compensatory rehabilitation using a special computer system controlling a light panel.

**Figure 2 figure2:**
[figure not shown]
Flow Chart.

The Neuro Vision Technology training program is then used to transfer visual scanning strategies into the real world while doing therapist-assisted walking, with the aim of making participant perform these strategies automatically. Thus, scanning strategies are gradually implemented, learned and improved by participant first being exposed to quiet and then more busy locations, like moving participants from small and quiet rooms at our training facility into for example shopping centers or to a busy road, where participants have to safely cross at traffic light junctions safeguarded by a therapist. Depending on individual needs training may also involve the use of public transport, safely riding a bicycle and exercises in order to safely move in the traffic. A re-test of 3 hours duration is performed 6 weeks after the Neuro Vision Technology course has been finished and 52 weeks after a participant’s inclusion in the study (Figure 2).

All participants receive Neuro Vision Technology course training and are tested at baseline and at the end of the study for primary and secondary endpoints; the time frame is expected to be 5 to 6 months for study participation for each participant, although the Neuro Vision Technology course is ended after 4 months (Figure 2).

### Primary Hypothesis and Endpoint

It is our main hypothesis that participants will increase awareness of their surroundings, will improve navigating their surroundings, and will be able to experience a greater quality of life – including reduced symptoms of both fatigue and depression.

At the start of the intervention, standardized route training (mobility route training) is performed that participants must be able to perform independently, this intervention is also known as Mobility Assessment Course [2,6]. Mobility Assessment Course performance is the primary endpoint inspired by a similar trial, where the protocol was published, but currently the trial seems to have been cancelled [2]. On the route there are a number of targets (stars) that participants should locate. Investigators measure the number of targets ignored by any participant. Ability to perform correct target identifications by comparing how many targets participants identify before and after the intervention is the primary outcome measurement.

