### Limitations

Before planning the current trial, for years we evaluated the number of eligible participants, and finding eligible patients have been difficult. Therefore, we have omitted using a control group, since this may double the number of needed participants.

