### Conclusion

This trial will evaluate the effects of Neuro Vision Technology rehabilitation therapy and provide answers to the efficacy of such treatment methods. Vision is the most important sense in humans; thus, even small permanent deficits can dramatically affect the quality of life and we hope to be able to improve compensatory treatments by our current investigation.

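### The primary endpoint route is also called training and is repeated on the same people without a control, so a significant change cannot be read as efficacy of the course

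*Protocol article*

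**What the plan says.** Under Primary Hypothesis and Endpoint, the article says of the start of the intervention that "standardized route training (mobility route training) is performed that participants must be able to perform independently, this intervention is also known as" the Mobility Assessment Course. It continues: "Mobility Assessment Course performance is the primary endpoint". The score is the number of stars found on the route, and "comparing how many targets participants identify before and after the intervention is the primary outcome measurement".

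Methods states that "the same subject is examined before and after the intervention". Blinding confirms a single group without controls. Statistical Analysis compares before with after by a Wilcoxon test at P < .05, so the null hypothesis is no change. The section on the intervention says that trained scanning is carried over to indoor mobility routes during the course.

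Two safeguards are offered. Participants says that, because the field loss is chronic, "participants will not experience significant spontaneous remission or deterioration". Blinding says that different people assess function before and after, as far as possible without earlier contact with the participant. On the missing control, Limitations says only that "we have omitted using a control group, since this may double the number of needed participants". The Conclusion says the trial will "provide answers to the efficacy of such treatment methods".

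**The concern.** As written, one label covers a training activity, an intervention and the primary outcome measure. Finding stars along a standardized route is a search task. Scores on such a task can rise because people know the task or the route, because they adapt to a stable deficit in daily life, or because they expect to do better. Without a comparison group, each of these sits in the same before/after difference as any effect of Neuro Vision Technology.

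What is at stake is the reading of the result. A P value below .05 would show that the score changed. Presented as an answer on efficacy, it would credit the training with whatever part of the rise came from elsewhere.

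**Working it through.** **Which rival explanations do the safeguards remove?**

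- Chronic field loss: the Introduction bases this on recovery of visual field deficits, which it places mainly in the first month. It speaks to spontaneous recovery of the field. The endpoint is functional search, which can improve while the field stays fixed; compensatory training itself assumes as much.
- Different assessors: this limits assessor expectation. It does not affect what the participant has learned or expects.
- Neither addresses familiarity with the task or route, or functional adaptation. Limitations gives the reason for having no control but draws no consequence for interpretation.

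**Does the sample size allow for practice?** Inputs from Sample Size Estimation: 40% of targets at baseline, 65% six weeks after the course, alpha .05, beta .2, n = 23. The method is not named. Comparing 65% with a fixed 40%, one-sided:

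n = (1.645·√(0.40·0.60) + 0.842·√(0.65·0.35))² / 0.25² = 23.3, so 24.

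Using only the variance at 65%: n = (1.645 + 0.842)²·0.65·0.35 / 0.25² = 22.5, so 23. A one-sided McNemar calculation with gains only also gives 22.5, so 23. The formulas that recover the stated figure thus compare with a fixed baseline or with no change. The whole 25-point rise (65 − 40) is assigned to the course.

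**How easily could practice alone reach significance?** This is an illustration. The article gives neither a practice gain nor an SD of individual change, so both are assumed. The SDs are 20, 30 and 41 points; 41 is the SD at which a two-sided paired t-test with n = 23 has 80% power for 25 points. The course effect is set to zero.

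With gain g and SD s, the noncentrality is (g/s)·√23, and the chance of a significant improvement is the probability that a noncentral t on 22 degrees of freedom exceeds 2.074. For g = 10 and s = 20, the noncentrality is 0.5 × 4.796 = 2.40, giving 63%.

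| Assumed practice gain | SD 20 | SD 30 | SD 41 |
|---|---|---|---|
| 0 points | 2.5% | 2.5% | 2.5% |
| 5 points | 21% | 12% | 8% |
| 10 points | 63% | 33% | 20% |
| 15 points | 93% | 63% | 39% |

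Simulated Wilcoxon tests agree within about 3 percentage points. The smallest mean gain that reaches P < .05 is 2.074·s/√23, which is 8.6, 13.0 and 17.7 points respectively. All three lie below the planned 25.

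**The case against.** The strongest reply has four parts.

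1. **The wording may be loose.** The sentence stands in the endpoint section, describes something participants must do unaided, and is followed by text on measurement. Training is described elsewhere and in other settings, and the indoor routes used in training are never identified as the test route. A reader might infer that the endpoint route is itself rehearsed, or that the stars stay in the same places. The article says neither, and such operational detail may well sit in the full protocol. This stands, and neither is claimed here. What remains is that the definition of the primary endpoint, as published, merges test and training.

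2. **The absence of a control is disclosed and explained.** This stands too. A reader might take the single-arm design as the error, but it is a stated choice made because eligible patients are hard to find. The unsupported step is the efficacy conclusion.

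3. **The interval may weaken memory.** The article puts the end of the course at about 4 months and the re-test 6 weeks later, with a further test 52 weeks after inclusion. Participants are expected to find only 40% of targets at first. This may well shrink a practice gain. It does not make practice separable from training.

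4. **The percentages rest on assumptions.** This is correct. Gains of 10 and 15 points are 40% and 60% of the whole expected rise, and SD 20 is the most favourable of the three SDs to the concern. At SD 41 the figures fall to 20% and 39%. A reader might take 63% or 93% as this trial's false-positive risk; the documents do not support that.

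**Conclusion.** The point holds in a limited form. The article describes its primary endpoint task as training and as intervention, repeats it on the same people without a control, tests it against no change, and promises an answer on efficacy. The safeguards it names leave practice, functional adaptation and participant expectation in the estimate, so a significant change cannot be attributed to the course.

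This conclusion follows from the text alone and does not depend on the illustrative percentages. Those show only that practice could matter: a 10-point gain would give significance in about 20% to 63% of trials across the assumed SDs, and a 5-point gain in about 8% to 21%. The size of any real practice gain is unknown. Nothing here implies that the training is ineffective.

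**What to change.** 1. **Endpoint section.** Describe the Mobility Assessment Course as an assessment only. State that the test route is kept out of training, and use equivalent star layouts at the successive tests, with their order counterbalanced across participants. This costs little and needs no extra participants. The downside is some added within-person variance where layouts differ in difficulty; counterbalancing evens this out on average but does not remove it. If this is already the practice, one sentence settles it.

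2. **Reporting and conclusion.** Report the before/after change with a 95% CI. Replace the efficacy promise in the Conclusion with an estimate of change after training without a control. Add to Limitations that practice, adaptation and expectation cannot be separated from the effect of the course. This costs only wording and a more modest claim. It is needed even if the layouts vary, because new star positions do not remove familiarity with the task, and a CI expresses sampling error only.

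Two further steps are not requested. Testing against a pre-stated practice allowance would need a figure that the documents do not provide. Analysing change by time from onset would be imprecise in about 23 people and would address adaptation rather than practice.
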